## Trial design

The original RAPID study design was a four-arm, superiority, randomised controlled trial (RCT) with a MAMS adaptive design with three candidate interventions (PREVAIL, SAFETEL and BrighterSide) included in stage 1 with a randomisation allocation ratio of 1:1:1:2 favouring TAU. A decision was made in April 2023 to remove the BrighterSide arm (see ‘Unplanned trial adaptations’ section below), resulting in a new treatment allocation of 2:2:3 favouring TAU. The pre-planned trial adaptations are an interim analysis on the primary outcome of any psychiatric hospital over 6 months using data from the first 385 PREVAIL, SAFETEL and TAU participants recruited with outcome data at the 6-month follow-up.

### Unplanned trial adaptations

Several important changes to the design occurred after the trial commenced, which were unplanned changes to the design. In line with the Adaptive Designs CONSORT Extension (ACE) statement [30], we report the unplanned changes in this protocol. All changes were approved by the funder, and where regulation was required, was approved by the Medicines and Healthcare Products Regulatory Agency (MHRA), the UK Research Ethics Committee (REC) and Health Research Authority (HRA).

In response to feedback from NHS crisis teams regarding the duration of care, the inclusion criteria was changed from ‘*Receiving care from a HBTT (referrals to HBTT Team are associated with increased risk of a psychiatric hospital admission in the near future)*’ to ‘*Currently receiving care from a Home-Based Treatment Team/Crisis team or have done so within the last 14 days, since referrals to HBTT/Crisis Team are associated with increased risk of a psychiatric hospital admission in the near future*’. In response to feedback from crisis teams regarding the patient population diagnoses, we was advised to include patients with a post-traumatic stress disorder (PTSD) or complex PTSD (cPTSD) diagnosis. As such the inclusion was changed to include patients with these diagnoses to ensure generalisability of the study findings to the crisis team patient population.

Since the initial development of this protocol, the BrighterSide smartphone app has been evaluated in a large study of 550 participants from the general population who reported suicidal ideation and results showed there was no significant improvement for the primary outcome of suicidal ideation in comparison to the waitlist control group [24]. In response to the new scientific data, the RAPID design was changed from a four-arm trial to a three-arm trial following removal of the BrighterSide intervention arm. The decision was made in conjunction with the RAPID trial Data Monitoring Committee (DMC), Trial Steering Committee (TSC), the study sponsor and the funder. The following changes were made to the design:i.Randomisation ratio changed from 1:1:1:2 favouring TAU to 2:2:3 favouring TAU.ii.Target sample size changed from 1235 to 1064 (not inclusive of the 54 participants randomised to BrighterSide at the time of dropping this arm) with no loss of power.iii.Number required for the interim analysis will change from the first 559 participants recruited with available primary outcome data to first 385 PREVAIL, SAFETEL and TAU participants with primary outcome data and provide 92% power.iv.Removal of the following exclusion criterion since it was relevant only to the BrighterSide app, ‘*visual impairment, severe enough to prevent engagement with the BrighterSide app as provision would be impossible on both financial and logistical ground*’.v.The RAPID trial was initially classified as a clinical trial of a medical device by the MHRA based on the inclusion of the BrighterSide smartphone app. Following removal of this intervention and on exit of the last participant allocated to BrighterSide in November 2023, the trial ceased to be a clinical trial of a medical device and under the regulation of the MHRA.

All participants already recruited to the BrighterSide arm were followed up to 6-month follow-up and completed involvement as per the study protocol.

Our trial included an internal pilot. Following review of the internal pilot recruitment data by the funder in August 2023, the monthly recruitment target was reduced from 50 to 35 participants per month effective from June 1, 2023.

## Methods: participants, interventions and outcomes

### Study setting

RAPID is conducted in UK NHS crisis services, which are typically referred to as Home-Based Treatment Teams (HBTT) across five locations in England and Scotland. The five settings are East London NHS Foundation Trust, NHS Greater Glasgow and Clyde, Greater Manchester Mental Health NHS Foundation Trust, Northeast London NHS Foundation Trust and Oxford Health NHS Foundation Trust. Participant assessments take place in community settings including the home of the participant or at a community clinic. All interventions are delivered remotely via videoconference or by telephone. Full details of the study sites can be found at our ISRCTN record: 10.1186/ISRCTN33079589. We use SPIRIT reporting guidelines for this protocol [31].

### Eligibility criteria

Our inclusion criteria are as follows:Currently receiving care from a Home-Based Treatment Team/crisis team or have done so within the last 14 days, since referrals to HBTT/crisis team are associated with increased risk of a psychiatric hospital admission in the near futureAged 16+Meet criteria for a diagnosis of SMHP (schizophrenia spectrum, bipolar, major depressive disorder, emotionally unstable personality disorder (EUPD), PTSD or cPTSD) since these diagnoses account for the majority of PHAs for mental health difficultiesExperienced suicidal ideation or attempt within the last month/current crisis episode, as operationalised by answering ‘yes’ to items 1 or 2 of the Columbia-Suicide Severity Rating ScaleAble to provide informed consentReceiving care from a Community Mental Health Team or Early Intervention Service, to ensure ongoing specialist mental health support following discharge from HBTT

Our exclusion criteria are as follows:Organic impairment, as this could be the cause of mental health symptoms rather than a SMHP.Non-English speaking, since two of the interventions are remotely delivered talking therapies and one of the interventions is a smartphone app which has only been developed in English. Provision for non-English speakers would be impossible on both financial and logistical grounds.Primary diagnosis of a drug or alcohol dependence, as this could be the cause of mental health symptoms rather than a SMHP.Moderate to severe learning disability as confirmed by the participant’s responsible clinician in their care team.For both ethical and safety reasons, immediate risk to others as confirmed by the participant’s responsible clinician in their care team.Currently receiving psychiatric inpatient care (since people in recent contact with crisis teams may have already been admitted to hospital).

### Who will take informed consent?

Informed consent is obtained from potential trial participants by Research Assistants (RA) at each of the five sites. RAs are trained in Good Clinical Practice (GCP) and are supervised by the site Principal Investigators. Potential participants are provided with a REC-approved Participant Information Sheet (PIS) and are given at least 24 h to consider the information before providing informed consent. We prioritise recording informed consent in writing via a wet-ink signature from both the participant and the researcher. However, where it is not feasible to seek a wet-ink signature from the participant on paper forms, i.e. when a potential participant is extremely clinically vulnerable to COVID-19 and risks of meeting in-person are significant, informed consent is taken via a remote method (telephone or videoconference). As approved by the study sponsor, the REC and HRA, the consent visit is audio recorded and the audio recording is retained in the Trial Master File as evidence of the informed consent process. For audio-recorded consent, the participant is required to state their full name and date of consent, the researcher reads out each statement on the consent form and in return the potential participant verbally confirms their agreement with each statement of consent, the researcher adds their wet-ink signature to the consent form as evidence of their taking consent and where possible, a wet-ink signature is sought from a participant at a later date. All participants are provided with a copy of their consent form.

## Interventions

### Explanation for the choice of comparators

The control condition is TAU, consisting of multi-disciplinary care delivered by crisis teams. Different psychosocial interventions are recommended in National Institute for Health and Care Excellence guidelines for the different diagnostic groups, so there is no single active comparator that would be suitable. TAU services are not asked to withhold any treatment and all routine or additional treatments are monitored via the Economic Patient Questionnaire, which tracks access to health and social care services.

### Intervention description

#### SAFETEL

SAFETEL is a brief, psychosocial intervention delivered by Assistant Psychologists (APs) employed by the NHS and delivered by telephone or videoconference [19, 20]. Participants allocated to the SAFETEL intervention are offered up to 12 sessions of the intervention over a 3-month intervention period. In the initial phase of delivery, a safety plan is developed collaboratively. It has six components: (i) identifying warning signs of an impending suicidal crisis; (ii) utilising internal coping strategies; (iii) engaging social contacts and social settings to distract from suicidal thoughts; (iv) contacting social supports for assistance in resolving the suicidal crisis; (v) contacting mental health professionals; (vi) minimising access to lethal means. The suitability, barriers and likelihood of employing these strategies during a suicidal crisis are explored, as well as examples of such strategies being provided. Follow-up contacts are provided over a period of 3 months. The follow-up calls comprise three components: (1) suicide risk assessment and mood check; (2) review of the participant’s safety plan, with revisions made if required; (3) supporting treatment engagement through exploration of barriers to engagement, motivational enhancement, problem-solving and support. The core element of SAFETEL is the collaborative development of the safety plan (within the 1st session). This is a prioritised list of coping strategies and supports that individuals can use during or preceding suicidal crises. It has been developed to also address challenges in continuity of care across vulnerable transitions. SAFETEL incorporates telephone follow-up to conduct periodic risk assessment and mood checks. This allows for the continuous review of the safety plan and provides opportunities to problem-solve obstacles to treatment and help with linkage to services, if necessary. It actively incorporates evidence-based suicide prevention strategies, including facilitation of problem solving and coping skills, identification and use of social supports and emergency contacts, lethal means restriction, service linkage and motivational enhancement to promote community treatment engagement.

#### PREVAIL

PREVAIL is a brief, psychosocial intervention delivered by Peer Support Workers (PSWs) employed by the NHS and is delivered by telephone or videoconference [25]. Participants allocated to the PREVAIL intervention are offered up to 12 sessions of the intervention over a 3-month intervention period. The key components of the PREVAIL intervention include common elements of peer support (PS) such as supportive listening and PSW sharing recovery stories, improving hope and belongingness, managing acute suicide risk including safety planning, maintaining both peer and PSW wellness and principles of motivational interviewing. PREVAIL is delivered in three phases: (i) assessment and getting to know you, (ii) active involvement and (iii) ending and consolidation.

Semi-structured conversations incorporate suicide prevention strategies derived from CBT and motivational interviewing (MI), including goal setting, distress tolerance, and increasing optimism and social connectedness. These conversations use a standardised format including the steps of Invite, Learn, Share and Motivate. In the Invite step, permission is sought from the participant to have a conversation about a hope or belongingness-related topic. During the Learn step, information regarding what the participant has already tried and what the participant thinks might be helpful or relevant to their situation is elicited. During the Share step, helpful suggestions are made based on the PSW’s personal experience or knowledge. The Motivate step engages the participant in ‘change talk’, including how acting might be helpful to them and how they might implement changes.

The final phase, focusing on endings, consolidation and future directions (including future access to peer support), will span sessions 11–12 (approximately), although endings and the time-limited nature of PREVAIL will be regularly discussed throughout all phases. The PSW may transition to a step-down phase at session 10 by moving to fortnightly contact. The aim of the final sessions is to consolidate learning, review what has been helpful and develop a plan to maintain gains. The format of delivery will be flexible throughout the 12 sessions.

The PS values of shared lived experience; reciprocity and mutuality; validating experiential knowledge; choice and control; discovering strengths and making connections are core to delivery. It is expected that peer relationships will offer emotional and instrumental support and promote hope through role modelling. PSWs will offer validation of the person’s suicidal experiences and concerns by showing understanding through their own experiences and enabling the participant to engage in talking about their experiences and concerns relating to suicide and hopes for the future.

#### BrighterSide smartphone app

BrighterSide is a self-guided smartphone app to help those with suicidal thinking to understand their thoughts and develop the best skills and strategies to help manage them [24]. The app contains five modules that are primarily based on CBT and DBT. The module topics are (1) Understand Your Thoughts; (2) Prevent a Crisis; (3) Navigate your Emotions; (4) Navigate Your Thoughts; and (5) Plan for the Future. BrighterSide allows users to personalise their experience with the following key features: develop a personalised safety plan, daily check-ins to help users connect with their feelings (this option can be skipped), coping tools including claiming and distracting techniques, pathway selection through the app based on the user’s preference and favourites to allow users to save their favourite activities and content. Content is not time-gated, with all five modules available immediately on installation and can choose which pathway or activities they wish to complete.

All participants allocated to BrighterSide are provided by the study team with a smartphone with the BrighterSide app installed and the app is activated by the participant with an access code provided by the study team as part of onboarding. Onboarding and offboarding is by a study AP or other non-blind member of the trial team. Access to BrighterSide app is exclusively for use in a clinical trial and access is removed on exit from the study. Participants can email themselves a copy of their safety plan from within the app at any time and at offboarding. BrighterSide collects usage data that facilitates monitoring of fidelity and adherence with the intervention. Adherence is defined as engagement with at least two of the five modules.

There are no criteria for discontinuing or modifying allocated interventions.

### Training and supervision

PSWs require a minimum of at least 1-year experience as a PSW and to have completed a formal PS qualification/course. APs are required to have a bachelor’s degree in psychology or another related discipline and experience of working in a health and social care setting. APs and PSWs are NHS employed (either substantive or honorary contracts); receive training in the intervention manual and NHS mandatory training (including safeguarding vulnerable adults) and receive weekly supervision from a clinical psychologist that covers clinical issues and fidelity. PSW and APs are required to role play delivery of interventions to a satisfactory/competent standard prior to delivery to trial participants. To ensure ongoing reflective learning, consistency across sites and fidelity to the manual APs and PSW attend an intervention specific, group supervision. Both SAFETEL and PREVAIL involve safely addressing suicidal crises and participants are ask about suicidal thoughts or behaviours at each encounter. If endorsed, the AP or PSWs use a scripted risk formulation assessment algorithm to gather additional information regarding any recent suicidal behaviours, whether suicidal ideation has worsened since the thoughts were last discussed with a clinician and the person’s level of intent to act upon their thoughts. If any of these risk factors are present, the AP or PSW immediately contacts the mental health clinician on-call for the RAPID study to review the assessment with the patient still present, and it would be the clinician’s responsibility to determine the necessary next steps to ensure safety.

### Strategies to improve intervention fidelity and adherence

For both SAFETEL and PREVAIL, fidelity to delivery is checked by listening to audio recordings of the intervention sessions. Feedback is given to staff with opportunities for further refresher training if required. For SAFETEL, 20% of the initial safety planning sessions for which we have recordings will be checked for fidelity against a standardised rating scale of fidelity [20]. These will be double coded by another team member and tested for inter-rater reliability. Adherence to SAFETEL is defined as attending the initial safety planning session and at least one follow-up call as this was the definition of adherence provided by the developers of SAFEEL in their pilot work. For PREVAIL, fidelity will be monitored the fidelity checklist to ensure the conversation structure of Invite, Learn, Share and Motivate (ILSM) [25]. Adherence to PREVAIL is defined as attending at least PREVAIL sessions.

### Relevant concomitant care permitted or prohibited during the trial

Our participants are patients, whom at consent, are under the care of a community mental health team and/or have recently been under the care of a crisis team, which typically includes some or all the following: provision of care coordination from a Community Psychiatric Nurse, Social Worker or Occupational Therapist, outpatient psychiatry and access to psychology in accordance. In England, this delivery is in line with the National Institute for Health and Care Excellence (NICE) guidelines and in Scotland access to psychological interventions is in line with Matrix Guidelines relevant for the participant’s mental health condition. As it would be unethical to restrict access to treatment as usual for our participants, we do not prohibit any of the care provided by the treatment as usual services for the different diagnostic groups, so there is no single active comparator that would be suitable.

### Provisions for post-trial care

There is no provision for post-trial care from the research team. Participants have access to TAU, which as outlined is access to a secondary care community mental health service, or if discharged from secondary care they have access to primary care support including a General Practitioner and the national UK NHS helpline 111. All participants are offered a helpline card with local and national statutory (NHS) and non-statutory (voluntary) services that can offer support in a crisis. This is offered throughout the trial and on exit.

### Outcomes

#### Primary outcome

The primary outcome is any admission to a psychiatric hospital admission over 6 months (treated as a dichotomous yes/no variable) which is obtained by screening the participants’ electronic patient records (EPR).

#### Secondary outcomes

The secondary outcomes listed are collected by RAs at baseline, 3-month and 6-month assessment:Suicidal thoughts and behaviours are assessed using the Columbia-Suicide Severity Rating Scale (CSSRS), which is a valid and reliable interviewer rated measure [32, 33]. As the CSSRS is an interview-based measure with assessors rating participant responses for each CSSRS item, we require all assessors to undergo training in delivery of the interview and scoring is checked for reliability against a gold standard provided by an expert assessor ([name]). Training for the CSSRS is provided by an expert in the field of suicide intervention research ([name]) and all RAs are required to complete two CSSRS role plays with the trial management team to ensure proficiency of clinical skills (warmth, non-judgmental stance, active listening) and skill in asking the required questions as per the CSSRS interview schedule.Personal recovery using a service-user defined self-report measure of recovery, The Process of Recovery Questionnaire [34].Health status using the EQ-5D-5L self-report measure, which is a health status questionnaire shown to have acceptable validity in people with schizophrenia in European countries [35].The Recovering Quality of Life (ReQoL-10) self-report measure, which focuses on aspects of recovery and quality of life and was designed for use in a broad range of mental health conditions. It was collaboratively developed with service users and clinicians [36].Wider NHS and social care use will be assessed by the Economic Patient Questionnaire, which is conducted in an interview format and completed from the participants self-report regarding use of NHS and social care services. It also includes the Psychiatric Hospital Record, completed from the EPR [37].Anxiety will be measured using the GAD-7 a self-report measure [38].Depression will be measured using the PHQ-9 a self-report measure [39].Hope will be measured using the Adult HOPE Scale, which is an 8-item self-report questionnaire [40].Entrapment will be measured using the 4-item self-report Entrapment Scale Short-Form [41].Self-reported potential adverse effects of study participation measures on exit from the study at 6-month assessment [42].

We record and report all adverse events (AEs) and serious adverse events (SAEs) for each participant for the 6-month period that they are enrolled in the study. We are made aware of AEs and SAEs though the following sources: self-report from the participants, report from the participants care team and reports documented in the EPR and identified during the EPR screening for the primary outcome. Full details of AE and SAE definitions and reporting can be found below.

### Participant timeline

A time schedule of enrolment, interventions, assessments and visits for participants are in Table 1.

**Table 1 Tab1:** Schedule of schedule of enrolment, interventions and assessments

**Time point**	**Enrolment** **−t1**	**Allocation** **0**	**Post-allocation**					
			**Month 1**	**Month 2**	**Month 3**	**Month 4**	**Month 5**	**Month 6**
**Enrolment**								
Informed consent	**X**							
Baseline assessment	**X**							
Allocation		**X**						
**Interventions**								
PREVAIL			**X**	**X**	**X**			
SAFETEL			**X**	**X**	**X**			
BrighterSide			**X**	**X**	**x**			
**Assessments**								
PHR	**X**				**X**			**X**
CSSRS	**X**				**X**			**X**
QPR	**X**				**X**			**X**
EQ-5D-5L	**X**				**X**			**X**
ReQoL-10	**X**				**X**			**X**
EPQ	**X**				**X**			**X**
GAD-7	**X**				**X**			**X**
PHQ-9	**X**				**X**			**X**
AHS	**X**				**X**			**X**
ESSF	**X**				**X**			**X**
Learning from You								**X**
Adverse events^a^								**X**

*AHS* Adult Hope Scale, *CSSRS* Columbia-Suicide Severity Rating Scale, *EPQ* Economic Patient Questionnaire, *EQ-5D-5L* Health Status, *ESSF* Entrapment Scale Short-Form, *GAD-7* General Anxiety Disorder Scale 7-item, *PHR* Psychiatric Hospital Record, *PHQ-9* Patient Health Questionnaire 9-item, *QPR* The Process of Recovery Questionnaire, *ReQoL-10* The Recovering Quality of Life Questionnaire

^a^Adverse events will be monitored at each time point and at every intervention session

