## Objectives

Our primary objective is to answer the question of which brief, remote psychosocial intervention for people with SMHPs who report recent suicidal ideation, or a suicide attempt is most clinically effective and cost-effective in preventing avoidable PHAs in comparison to TAU, and to determine the safety of the interventions.

Specific hypotheses are that, compared to TAU, our brief, remote interventions plus TAU will lead to:Reduction in psychiatric hospital admissions over 6 months (primary outcome)Reduction in psychiatric hospital admissions over 3 monthsReduction in suicidal ideation over 3 and 6 monthsImprovement in user-defined recovery and quality of life over 3 and 6 months

We also hypothesise that our interventions will be cost-effective over 6 months in comparison to TAU.

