### Adverse event reporting and harms

An adverse event (AE) is defined as any untoward medical occurrence, unintended disease or injury or any untoward clinical signs (including an abnormal laboratory finding) in subjects, users or other persons whether or not related to the research procedures or intervention. This definition includes events related to the study interventions and events related to the procedures involved. A serious adverse event (SAE) is defined as an adverse event that: (1) results in death, (2) is life-threatening, (3) requires hospitalisation or prolongation of existing hospitalisation, (4) results in persistent or significant disability or incapacity, (5) consists of a congenital anomaly or birth defect, or (6) is another important medical event if determined to be serious based on medical judgement. Data on adverse and serious adverse events will be collected via three sources (1) participant self-report (to a study team member), (2) identification through EPR screening for the primary outcome data or risk updates ahead of assessments or intervention sessions, and (3) we may become party to an adverse event during contact with a participants care team. Study team members are required to report all adverse and serious adverse events in line with our trial standard operation procedure for AEs for all participants from the time of their enrolment into the study as defined as the time at which a participant sign and dates the informed consent form.

AEs and SAEs are reviewed by the study CI or another delegated clinician to determine severity, intensity, causality and expectedness. Thoughts of suicide are associated with increased rates of suicide [50] and between 25 and 58% of people who report suicidal ideation will make a suicide attempt amongst those with suicidal ideation, between 25 and 58% will make a suicide attempt [51]. In line with previous trials, expected adverse events include worsening of symptoms defined as an increase in severe suicidal thoughts or a suicide attempt [24].

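### Adverse events are sought at every intervention session, contacts that TAU participants do not have, so recorded event counts by arm are not like for like

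*Protocol article*

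**What the plan says.** The Objectives section makes safety part of the primary objective: "to determine the safety of the interventions". The section on the data monitoring committee (DMC) has its closed session review safety data by treatment group.

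Collection is described in three places.

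- Table 1, footnote a: "Adverse events will be monitored at each time point and at every intervention session".
- Adverse event reporting and harms names three sources: "participant self-report (to a study team member"; "identification through EPR screening for the primary outcome data or risk updates ahead of assessments or intervention sessions"; and contact with the participant's care team.
- Training and supervision, on SAFETEL and PREVAIL delivery: "participants are ask about suicidal thoughts or behaviours at each encounter". A positive answer leads to scripted questions on recent behaviour, worsening and intent.

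The harms section also states that "expected adverse events include worsening of symptoms defined as an increase in severe suicidal thoughts or a suicide attempt". What is asked at each session is therefore itself an expected adverse event.

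On the number of sessions: "Participants allocated to the PREVAIL intervention are offered up to 12 sessions of the intervention over a 3-month intervention period". The SAFETEL section says the same of its own arm. TAU is crisis-team care without study sessions. All arms have assessments at baseline, 3 and 6 months.

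**The concern.** A comparison of adverse event counts between arms is fair only if events have about the same chance of being found in each arm. Here the chance depends on allocation. Staff in two arms ask repeatedly about the events of most interest in this population, and study team members must report what they learn. TAU has no matching contact during the treatment months.

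If the true risks were equal, PREVAIL and SAFETEL would still be expected to show more recorded events. The DMC could see a harm signal that reflects detection alone, or could put a real excess down to extra detection. The Discussion lists adverse event recording among the measures taken to minimise bias, but the article does not acknowledge this difference between arms. The primary outcome is not affected.

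**Working it through.** The plan states no figure on this point, so there is none to reproduce. The check has three parts.

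**1. Scheduled study contacts after allocation**

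- All arms: assessments at 3 and 6 months = 2.
- PREVAIL or SAFETEL: up to 12 sessions, so up to 2 + 12 = 14, and 14 / 2 = 7.
- A participant who attends two sessions (the PREVAIL adherence threshold): 2 + 2 = 4, and 4 / 2 = 2.

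These are counts of contacts, not of events detected.

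**2. Sources compared across arms**

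- *Self-report to a study team member.* In TAU this occurs mainly at two assessments. In the active arms it also occurs at sessions with direct questioning. Clearly unequal.
- *Electronic patient record.* The primary-outcome screen covers the six months in every arm. Checks before sessions exist only in the active arms, but an event already in the record would also be seen at the later screen, so they mainly bring detection forward. Roughly equal, with one reservation: the blinding section requires interventionists to pass reported risks to the care provider, so a session disclosure may create a record entry that would not exist under TAU.
- *Care-team reports.* Available in all arms.
- *Columbia scale (CSSRS).* Given in all arms at 3 and 6 months by assessors blind to allocation. Equal by design.

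The unequal part is therefore mainly self-reported or non-serious events, ideation, and attempts that reach neither the record nor the assessments.

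**3. Illustration of size (assumed inputs)**

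The documents give no event risks or detection probabilities. Let the true risk p be the same in both arms, with detection probability d_T in TAU and d_A in an active arm.

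- Recorded risks: p × d_T and p × d_A.
- Recorded risk ratio: d_A / d_T.
- Arm sizes, taking 2:2:3 of 1064: 1064 × 3/7 = 456 for TAU and 1064 × 2/7 = 304 per active arm. This is approximate, because early allocation was 1:1:1:2.
- Chance of a nominal two-sided p < 0.05 against the active arm: Φ[(D − 1.96 × SE0) / SE1]. D is the difference in recorded risks, SE0 the pooled and SE1 the unpooled standard error.

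Worked case: p = 0.30, d_T = 0.70, d_A = 0.90.

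- Recorded risks 0.21 and 0.27, so D = 0.06 and the ratio is 0.90 / 0.70 = 1.29.
- Pooled risk (456 × 0.21 + 304 × 0.27) / 760 = 0.234.
- SE0 = √[0.234 × 0.766 × (1/456 + 1/304)] = 0.0313.
- SE1 = √[0.21 × 0.79/456 + 0.27 × 0.73/304] = 0.0318.
- Φ[(0.06 − 1.96 × 0.0313) / 0.0318] ≈ 0.48.

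| Detection, TAU v active | Recorded risk ratio | Chance of false signal, p = 0.10 | Chance of false signal, p = 0.30 |
|---|---|---|---|
| 90% v 95% | 1.06 | 4% | 7% |
| 70% v 90% | 1.29 | 18% | 48% |
| 50% v 90% | 1.80 | 58% | 98% |

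With equal detection, the chance of a false signal in this direction is 2.5%. The effect runs from negligible to large within assumptions that the documents cannot narrow.

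**The case against.** **No between-arm analysis of adverse events is specified in the article.** Collection follows a separate operating procedure, and a detailed analysis plan is to follow. Neither is shown, and detection source may already be recorded. That stands as a limit: the point cannot be that source recording is absent. But the unequal collection schedule is stated in the article itself, as are the safety objective and the review by arm.

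**The events of concern are also measured equally in all arms.** A reader might infer that a real harm could never be separated from extra detection. The documents do not support that. The blinded CSSRS at 3 and 6 months, admissions from the record and the exit measure of adverse effects all give a symmetric check.

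**Pre-session record checks look like a second large source of bias.** A reader might infer this from the harms section, but the six-month screen reads the same records in every arm.

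**Seven-fold contact might be read as seven-fold bias.** It is the maximum number of contacts and says nothing direct about events found.

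**Asking about risk is part of both interventions, and any bias runs against them.** Both are true. Some asymmetry is unavoidable, and it would not make an active arm look falsely safe. It can still mislead in the other direction, and it can weaken the reading of a true excess.

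**A restricted comparison could hide session-only events from the DMC.** This is a fair objection to dropping them, so the all-source table should stay.

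**Conclusion.** The concern holds in a limited form. As written, the plan finds adverse events with unequal intensity: up to 14 scheduled study contacts in PREVAIL and SAFETEL against 2 in TAU, with direct questioning about the trial's own expected events. The expected direction is more recorded events in the active arms at equal true risk. Deaths and psychiatric admissions should be little affected.

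The size is unknown. The illustrative ratios of 1.06 to 1.80 rest wholly on assumed detection probabilities and are not estimates for this trial. The direction assumes that some events disclosed at sessions would otherwise go unrecorded. BrighterSide was self-guided, so the point mainly concerns the two remaining active arms.

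This should be addressed, because it bears on a stated objective.

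**What to change.** 1. Record prospectively, for every adverse and serious adverse event, how it was first detected: session, pre-session check, 3- or 6-month assessment, record screen, or care team. This may be hard to reconstruct later.
2. In DMC reports and the final paper, keep the all-source table by arm.
3. Add a between-arm comparison restricted to sources common to all arms: the record screen over the fixed six months, and the 3- and 6-month assessments including the CSSRS. Name it in advance as the main basis for comparative safety conclusions.
4. Show session-only events separately, by arm.
5. State that this reduces the bias but does not remove it, because risks disclosed at sessions are shared with care providers and may enter the record.

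Session monitoring and the handling of individual safety concerns do not change. The cost is one extra field on the adverse event form, if it is not already there, and one extra table.
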